### Randomization

In each center, the enrolled patients will be randomly assigned to the control group of conventional treatment, the preoperative-Danhong group, or the postoperative-Danhong group, allocated by the central randomized management system according to a ratio of 1:1:1. The randomization sequence will be generated in varying block sizes and stratified by center. After informed consent is obtained, the researcher will log into the central randomized management system of the network and choose the center as the stratified factor. The central randomized management system will generate a unique identification code and random number for each patient, which can be used to represent the identity of the patient and indicate the therapeutic intervention.

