### Intervention

Patients will receive aspirin 300 mg and clopidogrel 600 mg (or ticagrelor 180 mg) before PCI. Postoperative treatments will include antithrombotic medication (aspirin 100 mg daily with clopidogrel 75 mg daily or ticagrelor 90 mg twice daily), anti-myocardial ischemia (β-blockers, nitrates, calcium antagonists), inhibition of cardiac remodeling (angiotensin-converting enzyme inhibitor, angiotensin receptor blocker, aldosterone receptor antagonist), and lipid control (atorvastatin 20 mg daily). These are all serving as conventional treatment for patients with STEMI. Patients in the preoperative-Danhong group will additionally receive Danhong Injection treatment (40 ml with 250 ml of saline, intravenous drip infusion) as early as possible before PCI and continue to the seventh day, once per day. Patients in the postoperative-Danhong group will additionally receive Danhong Injection treatment (40 ml with 250 ml of saline, intravenous drip infusion) right after PCI and continue to the seventh day, once per day.

It should be noted that any Chinese medicine related to the treatment of coronary heart disease should not be taken orally, intravenously, or intracoronally during the study. According to the hospital centralized monitoring data [27], the following drugs should be avoided in combination with Danhong Injection: potassium magnesium aspartate, thymosin, celecoxib, and bisoprolol fumarate. The patients will stay in the hospital during the intervention period, which is convenient to monitor adherence to the intervention.

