It will be the first and largest well-designed, multicenter randomized controlled trial with rigorous quality control to evaluate the efficacy and safety of Danhong Injection for MVO prevention in patients with STEMI.No previous research has evaluated the optimal intervention timing of TCM medications during the perioperative period of PCI, and our trial will fill that gap.

As for the limitations, a placebo-controlled and double-blind method will not be applied in this trial, which may bias the results. We choose to use a blank control group mainly because the preoperative-Danhong group and postoperative-Danhong group need to share a common control for the purpose of identifying the optimal timing of intervention. It is not possible to start placebo use at two different time points in one group, not to mention that it is hard to make the Danhong Injection placebo with the same color. However, this study applies an evaluator-blind method to reduce evaluation bias. In addition, the intensive evaluation time points bring difficulty to trial implementation. We will strengthen the SOP training and monitoring to ensure the soundness of the process.

This study will be the first and largest well-designed, multicenter randomized controlled trial with rigorous quality control to evaluate the efficacy and safety of Danhong Injection, as well as its optimal timing of intervention, to prevent MVO in patients with STEMI. The results of this trial will provide valuable clinical evidence for recommendations on the management of the disease and clues to the underlying mechanisms.

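### Postoperative-versus-control allocation is available at the site before PCI although nobody needs it until PCI ends, so avoidable performance bias can enter that comparison

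*Protocol article*

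**What the plan says.** The Protocol article's Randomization section describes a single draw to three arms, "allocated by the central randomized management system according to a ratio of 1:1:1", stratified by center. On timing it says: "After informed consent is obtained, the researcher will log into the central randomized management system". The system returns an identification code and a "random number for each patient, which can be used to represent the identity of the patient and indicate the therapeutic intervention". No second or delayed release is described.

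The Intervention section has the preoperative arm start Danhong "as early as possible before PCI and continue to the seventh day, once per day" and the postoperative arm "right after PCI and continue to the seventh day, once per day". All three arms share the same conventional treatment.

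On blinding, the Discussion states that "a placebo-controlled and double-blind method will not be applied in this trial, which may bias the results". It gives two reasons for having no placebo: a shared control cannot start placebo at two different times, and a colour-matched placebo is hard to make. The safeguard offered is that "this study applies an evaluator-blind method to reduce evaluation bias".

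**The concern.** Until the end of PCI, a postoperative-Danhong patient and a control patient are the same patient as far as the protocol is concerned. Knowing which is which at that stage serves no purpose in care, but it gives staff an opportunity to treat the two differently.

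The primary outcome is ST resolution of at least 70% at 90 minutes after PCI, so what happens during the procedure bears directly on it. The Background lists discretionary measures that have been tried against no-reflow, including thrombus aspiration, distal protection, glycoprotein IIb/IIIa antagonists, nicorandil and vasodilators. If their use depended on the known arm, the two groups would differ by more than Danhong. Central blinded reading of ECGs and angiograms prevents biased reading. It cannot undo a difference in what was done to the patient.

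Two results are exposed. One is postoperative versus control, which is listed second in the hierarchical tests and carries the started-after-PCI half of the stated purpose. The other is the primary comparison, in which the postoperative arm is half of the combined Danhong group.

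**Working it through.** **Does allocation precede PCI?** The Randomization section does not mention PCI, so this has to be inferred.

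1. There is one draw to three arms, made after consent (Randomization).
2. One arm must begin Danhong before PCI (Intervention).
3. Whoever starts that infusion must know the arm before PCI. As the draw is single and three-way, it is made before PCI for all patients.
4. The code can indicate the intervention, and no staged release is described. As written, the full allocation is therefore available to site staff before PCI.

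**Who needs it then?** Before PCI the only actionable distinction is preoperative Danhong or not. The distinction between postoperative Danhong and control becomes actionable when PCI ends.

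**Do the stated reasons for the open-label design cover this?** Both reasons in the Discussion concern a placebo. Withholding the postoperative-versus-control label until PCI ends needs no placebo, so neither reason applies.

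**How many patients would see a changed display?** 2/3 × 336 = 224. This counts patients whose pre-PCI display would change. It is not a count of biased results.

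**What could a shift do?** The documents give no size for any shift, so the values below are assumptions that show sensitivity. They are not estimates.

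Inputs: control rate 50%, two-sided 0.05, 336/3 = 112 per arm, and 20% loss giving 0.8 × 112 = 89.6 per arm (all from Sample size). Assume no drug effect and a shift *b* in favour of the postoperative arm only. The chance of a false finding for Danhong (nominal 0.025) is approximately

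Φ[(d − 1.96·SE₀)/SE₁], with SE₀ = √[p̄(1−p̄)(1/n₁+1/n₂)] and SE₁ = √[p₁(1−p₁)/n₁ + p₂(1−p₂)/n₂].

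Example, *b* = 0.05 and 112 per arm: p̄ = 0.525, SE₀ = 0.0667, SE₁ = 0.0666. Then (0.05 − 0.1308)/0.0666 = −1.21, and Φ(−1.21) = 0.113.

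In the combined group (2:1 against control) the same shift is diluted to *b*/2.

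| Assumed *b* | Post vs control, 112/arm | Post vs control, 89.6/arm | Combined vs control, 112/arm | Combined vs control, 89.6/arm |
|---|---|---|---|---|
| 2 points | 0.048 | 0.045 | 0.037 | 0.036 |
| 5 points | 0.113 | 0.098 | 0.063 | 0.058 |
| 10 points | 0.323 | 0.268 | 0.137 | 0.118 |

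The pairwise columns treat that test on its own. In the plan it is reached only after a significant combined result, and it is listed after preoperative versus control, so its actual rate under no drug effect would be lower. A shift in the opposite direction would hide a real effect. The halving holds only if the shift sits in the postoperative arm; a change in how controls alone are treated would enter the combined comparison undiluted.

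**The case against.** **The text does not say the operator is told.** This is right. The article says that a researcher logs in. Who hears the result, and when, could be settled in a full protocol or in procedures not shown. A reader might infer that the operator knows the arm; the documents support only that the allocation is available at the site and that no described safeguard withholds it. The point survives in that form because it addresses a stated choice: one draw, one disclosure, blinding of evaluators only.

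**The mechanism comes from the Background.** Also fair. The listed no-reflow measures have been tried elsewhere. The Intervention section names neither aspiration, distal protection, glycoprotein IIb/IIIa antagonists nor nicorandil as part of conventional treatment, and it mentions nitrates and calcium antagonists only after the procedure. The documents give no rate of use and no sign that use depends on arm. The route to bias is plausible but not shown.

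**The direction is unknown.** This stands. Operators might do more for controls because nothing further will follow, which would pull the comparison towards no difference. The false-positive figures above assume the reverse.

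**The limitation is already declared.** Only in part. The Discussion admits that the lack of double blinding may bias results, but the reasons it gives do not reach this component.

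**The remedy is partial and adds a step in emergency care.** True. It leaves the preoperative arm and the 90 minutes after PCI unprotected, and it adds a log-in just as postoperative Danhong is due. That limits the gain, but the part of the risk that is removed needs neither a placebo nor extra patients.

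**Conclusion.** The point holds as a weakness of design. The full allocation is available before PCI, two of the three arms are handled identically until PCI ends, and nothing described keeps the distinction from the operator. Performance bias can therefore enter postoperative versus control, and through it half of the combined Danhong group, in a way the evaluator blinding does not address and the placebo argument does not excuse.

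Its size cannot be stated. A reader might infer that bias does enter, or that it amounts to some number of points against the 20.2-point target. The documents support neither: they give no value for a shift and do not settle its direction. The table shows only that a modest imbalance, if it arose, would matter.

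Nor is this a failure of allocation concealment. Assignment is central, follows consent and uses varying block sizes, so the issue is disclosure after assignment.

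The conclusion rests on one inference, that the draw precedes PCI, drawn from the Randomization and Intervention sections together. It also assumes that no procedure outside the article already withholds the label.

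**What to change.** Keep the single 1:1:1 randomisation and its sequence, and release the result in two steps. Before PCI, the central system shows only *preoperative Danhong: yes* or *no*. When the end of PCI is entered, it shows postoperative Danhong or control for the *no* patients. The arm is fixed centrally at randomisation, so patients who die during PCI or do not complete it keep their assigned arm and remain in the intention-to-treat population. Sample size, significance level, tests and the treatments themselves are unchanged.

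If the full protocol or site procedures already withhold the label, a sentence in the Randomization section saying so is enough.

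The cost is one extra log-in at the end of PCI. A second staff member can do it as the procedure closes, so that the start of postoperative Danhong is not held up. The documents do not say whether the system can stage its display, so this needs checking. Recruitment began on 30 June 2019, so the change is an amendment that benefits only patients still to be enrolled; under the Ethical plan section, revisions need ethics approval and renewed consent.

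Comparisons with the preoperative arm, and care between PCI and the 90-minute ECG, stay open-label and should remain listed as a limitation.

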### Data collection and management

The data will be managed according to standard operating procedures (SOPs). The data from the paper case report form (CRF) will be entered and stored in the electronic data capture system. A specialized quality inspector will regularly review CRFs and monitor the data. Monitoring results should be presented to the principal investigator in each center, who is responsible for the accuracy, completeness, and timeliness of the data recorded. After blind review and confirmation that the established database is correct, the data will be locked, and no changes will be permitted.

### Statistical analysis methods

The null hypothesis is that the rate of STR ≥ 70% at 90 min after PCI will be the same for the combined Danhong group and the control group. The primary outcome analysis will use the Cochran-Mantel-Haenszel test to compare the rate of STR ≥ 70% at 90 min after PCI between the combined Danhong groups and the control group. If the result of this analysis is significant, hierarchical testing will be used to compare the preoperative-Danhong group with the control group, the postoperative-Danhong group with the control group, and the preoperative-Danhong group with the postoperative-Danhong group.

For other categorical variables, comparisons between treatment groups will be done using Fisher’s exact test or the chi-square test as appropriate. Continuous variables will be compared using the *t* test or Wilcoxon rank-sum test as appropriate. Chi-square or Fisher’s exact tests will be used to compare the frequency of AEs between groups.

The intention-to-treat population, including all randomized patients, will be used for all efficacy and safety analyses. All analyses will be performed using SAS version 9.4 software (SAS Institute Inc), with a two-sided *P* value less than 0.05 considered significant. No interim efficacy analysis will be performed.

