### Outcome

The primary outcome is the rate of STR ≥ 70% on surface electrocardiogram (ECG) at 90 min after PCI. The secondary outcomes are the degree of STR, TIMI flow grade, TIMI myocardial perfusion grade, LVEF, N-terminal prohormone brain natriuretic peptide, high-sensitivity C-reactive protein, and infarct size expressed as area under the curve for cardiac troponin I and for creatine kinase MB. The MACE (defined as a composite of nonfatal stroke, nonfatal MI, target lesion revascularization, urgent stent thrombosis, and all-cause death) will be recorded, as well as the hospital readmissions for heart failure or cardiac angina. Health quality will be assessed by using the 12-item Short Form Health Survey [28].

The safety outcomes include bleeding events measured with Platelet Inhibition and Patient Outcomes (PLATO) criteria within 48 h and 30 days, as well as adverse events (AEs) during the study period. Abnormal change in routine blood test results will also be monitored during the study. In addition, psychologic status and dietary patterns of patients will be collected as relevant indicators using the Hamilton Depression Scale [29] and the Food Frequency Questionnaire [30]. A study schedule and evaluation of outcomes are provided in Table 1. Centralized, blinded reviews of angiographic data and ECG recordings will be conducted by two physicians, respectively.

**Table 1 Tab1:** Outcome evaluation time points

Outcomes	Baseline	Preoperation	Postoperation (immediately)	30 min	60 min	90 min	6 h	12 h	18 h	24 h	36 h	48 h	72 h	7 d	30 d
Subject characteristics	•	–													
STR	•	–		•			–			•	–			•	–
TIMI flow grade TMPG	–	•		–											
LVEF	–									•	–			•	
cTnI, CK-MB	•	–					•							–	
NT-proBNP	•	–								•	–	•	–	•	
hs-CRP	•	–								•	–		•		
MACE	–														•
Hospital readmission	–														•
SF-12	•	–													•
Bleeding events	–											•	–		•
Adverse events	•														
Routine blood test	•	–													•
HAMD-17	•	–												•	
FFQ	•	–													

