### Sample size

Based on the results of the previous investigation [31–33], a sample size of 336 participants was estimated to provide 80% power to detect an absolute difference of 20.2% between the combined Danhong group and control in the rate of STR ≥ 70% measured at 90 min after PCI at a two-sided significance level of 0.05, assuming an STR ≥ 70% rate of roughly 50% for the control group and 20% loss to follow-up.

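### The primary test and its pairwise follow-ups name no patient-level baseline covariate; prespecified adjustment for baseline ST elevation and onset time could add a few points of power at almost no cost

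*Protocol article*

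**What the plan says.** The primary outcome (Outcome section) is the "rate of STR ≥ 70% on surface electrocardiogram (ECG) at 90 min after PCI". For its analysis, the Statistical analysis methods section states: "The primary outcome analysis will use the Cochran-Mantel-Haenszel test to compare the rate of STR" at or above the threshold between the combined Danhong groups and control. If that test is significant, "hierarchical testing will be used to compare the preoperative-Danhong group with the control group", then the postoperative group with control, then the two Danhong groups with each other. The section names neither the CMH strata, nor the test for the pairwise steps, nor any baseline covariate.

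The Randomization section uses one factor: "The randomization sequence will be generated in varying block sizes and stratified by center". Centre is therefore the natural CMH stratum, although the article does not say so.

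Two patient-level baseline values follow from other parts of the protocol. Eligibility requires ischemic symptoms within 12 h, so onset time must be established. Table 1 marks STR as an essential item at baseline, and STR cannot be computed without the baseline ST elevation.

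The Sample size section says that "a sample size of 336 participants was estimated" to give "80% power to detect an absolute difference of 20.2% between the combined Danhong group and control", "at a two-sided significance level of 0.05", with an STR rate of "roughly 50% for the control group and 20% loss to follow-up".

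**The concern.** A CMH test adjusts only for discrete strata, and the only stratification factor in the article is centre. As written, neither the randomization nor the confirmatory analysis uses any patient-level information, although two candidate predictors should already be available.

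If those variables predict who reaches 70% resolution, adjusting for them removes outcome variance that would otherwise blur the treatment comparison. The gain matters most in the pairwise steps. The trial's second aim is the best timing of the injection, and that answer rests on these steps, which have less power than the combined test. Prespecified adjustment also gives an estimate that takes account of chance imbalance in onset time or baseline ST elevation, which blocking within centre does not control.

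**Working it through.** **Inputs from the protocol.** Control rate 0.50; Danhong rate 0.50 + 0.202 = 0.702; two-sided α = 0.05; 336 patients at 1:1:1, so 112 per arm; 20% loss, so 112 × 0.8 = 89.6 evaluable per arm.

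**Input not in the protocol.** The prognostic strength of baseline ST elevation and onset time, taken as R² = 0 to 0.29. R² of 0.04 to 0.175 (c-statistic about 0.61 to 0.74) serves as the working range.

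**1. The plan's own figure.** With k treated patients per control and p̄ = (p₀ + k·p₁)/(1 + k), the number of controls is

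n = [1.96·√(p̄(1−p̄)(1+1/k)) + 0.842·√(p₀(1−p₀) + p₁(1−p₁)/k)]² / (p₁−p₀)².

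- Combined Danhong against control (k = 2, p̄ = 0.6347): n = 68, total 3 × 68 = 204, and 204/0.8 = 255. The unpooled variance gives 259 and the continuity correction 282.
- One Danhong arm against control (k = 1, p̄ = 0.601): n = 92, total 276, and 276/0.8 = 345. The unpooled variance gives 89 per arm, and 267/0.8 = 334.

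So 336 does not follow from the combined comparison to which the protocol attaches it; it lies close to a pairwise calculation. That is a separate matter. Here it explains why the combined test has power to spare.

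**2. Power without adjustment.** Power = Φ[(0.202 − 1.96·SE₀)/SE₁], with 89.6 controls:

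- Combined: SE₀ = √(0.2319 × 1.5/89.6) = 0.0623; SE₁ = √((0.25 + 0.2092/2)/89.6) = 0.0629; Φ(1.27) = 89.8%.
- One arm against control: SE₀ = √(0.2398 × 2/89.6) = 0.0732; SE₁ = √((0.25 + 0.2092)/89.6) = 0.0716; Φ(0.82) = 79.4%.

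**3. Power with adjustment.** The formula replaces n by n/(1 − R²). The simulation (4,000 runs; 90 controls with 179 or 90 treated; 8 assumed centres for CMH; one normal baseline score) compares CMH with covariate-adjusted logistic regression.

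| R² (assumed) | Effective controls | Combined, formula | Combined, simulated | One arm vs control, formula | One arm vs control, simulated |
|---|---|---|---|---|---|
| 0 | 89.6 | 89.8% | 89.9 → 89.8% | 79.4% | 78.8 → 78.5% |
| 0.04 | 93.3 | 90.9% | 89.8 → 90.8% | 81.0% | 79.3 → 80.6% |
| 0.10 | 99.6 | 92.6% | 89.7 → 92.1% | 83.4% | 80.2 → 83.1% |
| 0.175 | 108.6 | 94.5% | 89.6 → 93.7% | 86.5% | 80.2 → 86.6% |
| 0.29 | 126.2 | 96.9% | 89.8 → 96.7% | 91.1% | 80.3 → 90.0% |

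Across the working range the simulated gain is 1.0 to 4.1 points for the combined test and 1.3 to 6.4 points for one arm against control. The formula is slightly more generous at the top (4.7 and about 7 points). In patients, 336 analysed with adjustment are worth 336/0.96 = 350 to 336/0.825 = 407 without it.

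**4. Does the adjusted test hold its level?** This depends on the method.

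- Under the null, the simulation in step 3 gave 5.2 to 5.4% rejection for CMH, 5.4 to 5.5% for adjusted logistic regression and 5.7 to 5.9% for the standardized risk difference (Monte Carlo SE 0.3 to 0.4 points).
- A likelihood-ratio test with a fixed effect for every centre plus covariates rejected at about 5 to 7% with 8 to 15 centres and 7 to 9% with 30. The number of centres is an assumption, as the article does not give it.
- A centre-stratified CMH-type score test on covariate-adjusted residuals held about 4 to 6%. It kept most of the gain: one-arm power rose from about 80% to 80–82% at a log-odds slope of 0.55 per SD (c-statistic about 0.65) and to 86–88% at a slope of 1.05 (about 0.75).

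**The case against.** The strongest reply is that nothing here is wrong. CMH is valid and can match randomization stratified by centre. The combined test exceeds its 80% target by about 10 points. The size of any gain rests on an assumed prognostic strength. All of that stands.

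A reader might infer more than the documents support, in four ways:

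- **That covariates are ruled out.** The article is silent on the CMH strata and on the pairwise tests, and a full protocol or SAP may settle both. What can be said is that the named confirmatory test is CMH and that no patient-level covariate appears with it.
- **That power is certainly being lost.** At R² = 0 the gain is nil.
- **That baseline ST elevation must be prognostic because it is the denominator of STR.** Being in the denominator, or being measured with error, does not show that it predicts crossing 70%.
- **That chance imbalance invalidates the unadjusted test.** The 5% level already allows for it; adjustment improves precision.

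Two further objections limit the remedy. Recording of infarct territory is not stated anywhere, so its availability cannot be assumed. An ordinary logistic model with an indicator for each centre can exceed 5%, so part of its apparent gain could be inflation. That second objection changes the method to recommend, but not the case for adjusting. The power of the preoperative-versus-postoperative step is not sized here, because the protocol states no expected difference for it.

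**Conclusion.** The point holds as an efficiency improvement, not as an error. The confirmatory test and its follow-ups name no patient-level covariate, while two should be available without new measurement.

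At the protocol's design rates and loss, adjustment adds about 1 to 4 points to a combined test already near 90%, and about 1 to 6 points to each Danhong-versus-control test near 79%. These gains assume that the covariates explain 4% to 17.5% of the outcome variance, a range not taken from the documents. With no prognostic value, the simulated loss from adjusting was at most about 0.3 points. There is little to lose and possibly something to gain, chiefly in the pairwise tests.

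**What to change.** Before database lock, prespecify the following for the primary test and for every hierarchical step:

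- Adjust for baseline summed ST elevation and onset-to-randomization time. Add infarct territory only if the central ECG reading records it.
- Keep centre as the stratum, and state this.
- Use a test that holds the 5% level when centres are many or small, such as a centre-stratified CMH-type score test on covariate-adjusted residuals. Do not use a likelihood-ratio test with a fixed effect for every centre.
- Report a standardized risk difference with a robust 95% CI.
- Keep the plain centre-stratified CMH test as a sensitivity analysis.
- Do not adjust for pre-PCI TIMI flow. The preoperative arm may already be on treatment when flow is read, so it is not a clean baseline value.

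The cost is a change of wording and a little more programming. The covariates must be fixed in advance, and the gain may prove small.

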## Discussion

Over the years, efforts have been made to detect an effective strategy to prevent and alleviate MVO in time windows of STEMI treatment, but currently no treatment has convincingly been proven to be beneficial in a multicenter controlled randomized trial with clinical outcomes [17]. And it is uncertain that whether early drug intervention could improve coronary reperfusion in patients with STEMI for primary PCI [34]. Our primary purpose is to evaluate whether additional Danhong Injection use is superior to conventional treatment alone for the prevention of MVO in patients with STEMI undergoing PCI. Furthermore, we hope to find the optimal timing of Danhong Injection intervention, which would be helpful to improve the clinical effect of TCM medications and to guide rational drug use.

Several clinical trials have been carried out to evaluate the effectiveness of TCM for the prevention and treatment of no-reflow in recent years. A randomized, double-blind, placebo-controlled, multicenter clinical trial evaluated the no-reflow protective and long-term effects of Tongxinluo capsules for AMI. The trial researchers observed that the reduction of no-reflow incidence was time-dependent in the Tongxinluo group with statistical significance at 24-h reperfusion compared with the control group. The infarction area determined by single-photon emission computed tomography was reduced on day 7 and day 180 after STEMI in the Tongxinluo group compared with the control group [35]. Compared with oral preparation, Danhong Injection has an advantage in taking rapid effect in the short time window of myocardial reperfusion. Systematic reviews have found that Danhong Injection is associated with improvement of reperfusion and LVEF, as well as reduction of MACE in acute coronary syndrome when combined with PCI [20, 21].

STR based on ECG is the simplest clinical evidence of effective myocardial reperfusion in myocardial cells and has been confirmed to have predictive value [17, 36]. We are adopting ECG to assess the MVO as the primary outcome, considering it is noninvasive, which makes it easy to observe the reperfusion trends between the three groups. Also, blinded reviews of ECG recordings and angiographic data will be conducted by two physicians independently to avoid potential evaluation bias.

This trial has the following advantages:

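### Read as a fixed sequence, the follow-up tests allow a confirmatory preoperative versus postoperative test only after both timings beat control; the order costs power and adds no type I error protection beyond the pooled gate

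*Protocol article*

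**What the plan says.** The Statistical analysis methods section sets one primary comparison, with both Danhong arms pooled and set against control: "The primary outcome analysis will use the Cochran-Mantel-Haenszel test to compare the rate of STR ≥ 70% at 90 min after PCI". A significant result opens the follow-up tests: "If the result of this analysis is significant, hierarchical testing will be used to compare the preoperative-Danhong group with the control group". Two further comparisons complete the list, namely "the postoperative-Danhong group with the control group, and the preoperative-Danhong group with the postoperative-Danhong group". The threshold is general: "with a two-sided *P* value less than 0.05 considered significant".

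The Sample size section powers the pooled comparison only: "a sample size of 336 participants was estimated to provide 80% power to detect an absolute difference of 20.2" percentage points. The control rate is taken as about 50%, with 20% loss. Allocation is 1:1:1.

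On timing, the Discussion says "we hope to find the optimal timing of Danhong Injection intervention". It presents this as a further aim after superiority over conventional treatment. The Abstract also names optimal timing, and the Discussion lists it among the trial's advantages as a gap to be filled.

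**The concern.** In a fixed sequence, a non-significant step bars confirmatory testing of every later step. Preoperative versus postoperative stands last, behind both comparisons with control. The two timings differ most when one of them resembles control, and in that case one of the earlier steps will usually fail. If only the preoperative start works, the sequence stops at postoperative versus control. If only the postoperative start works, it stops at preoperative versus control.

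At stake is the confirmatory power for a stated secondary aim, and some power for postoperative versus control. An order can be worth such a price when it protects the type I error. Here the pooled gate already gives that protection.

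**Working it through.** **Inputs.** Control rate 50%, difference 20.2 points (so 70.2%), N = 336, 20% loss, two-sided 0.05 (Sample size); 1:1:1 (Randomization). Per arm: 336/3 = 112 with no loss, and 112 × 0.8 = 89.6, about 90, after loss. All rates other than 50% and 70.2% are assumptions.

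**The plan's own figure.** For a 1:1 comparison of two arms with unpooled variance, n = (1.960 + 0.842)² × [p₁(1−p₁) + p₂(1−p₂)] / d² = 7.849 × (0.2500 + 0.2092) / 0.0408 = 88.3, so 89. Then 89/0.8 = 111.25, so 112, and 3 × 112 = 336. The stated total thus matches a pairwise calculation. For the pooled 2:1 comparison that the section names, 336 less 20% gives about 90% power rather than 80%. This is a separate matter; it is used here only to fix 90 to 112 per arm.

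**Does the order protect the error rate?** Call the pairwise nulls H1 (pre = control), H2 (post = control) and H3 (pre = post).
1. Any two of them imply the third, so every intersection is the global null that all three rates are equal.
2. The pooled null (average of the two timings = control), combined with any one of H1 to H3, also gives the global null.
3. The pooled test is a 0.05 test of the global null. By closed testing, each pairwise null may be tested at 0.05 once the gate is passed, in no order.

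Family-wise error with parallel tests after the gate, 90 per arm: 5.3% with all rates at 50% (the gate's own discrete size, which the sequence shares; 4.9% at 112 per arm), 4.5% with pre = post = 70.2%, and about 2% with one timing equal to control. Every rejection under the sequence is also a rejection in parallel.

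**Power.** Pooled-variance z tests at two-sided 0.05, without centre strata. Sequence: gate, pre vs control, post vs control, pre vs post. Parallel: gate, then each pair. Each cell gives 90 / 112 per arm.

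Chance of a significant pre vs post result:

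| Control/pre/post (%) | Gate passes | Pre vs post, no gate | Sequence | Parallel |
|---|---|---|---|---|
| 50/70.2/50 | 35% / 42% | 80% / 87% | 0.8% / 1.3% | 28% / 36% |
| 50/80/60 (assumed) | 89% / 95% | 84% / 91% | 17% / 27% | 75% / 86% |
| 50/90/70 (assumed) | >99% / >99% | 93% / 97% | 73% / 84% | 93% / 97% |

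Chance of a significant post vs control result:

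| Control/pre/post (%) | Sequence | Parallel |
|---|---|---|
| 50/70.2/70.2 | 69% / 79% | 79% / 87% |
| 50/50/70.2 | 2% / 3% | 35% / 42% |

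**Where the power goes at 50/70.2/50%, 90 per arm.** The gate takes the timing test from 80% to 28%, a loss of 52 points. The order takes it from 28% to about 1%, a loss of 27 points. Of the 35.3% of trials that pass both the gate and pre vs control, only 2.2% of all trials also pass post vs control, so 1 − 0.022/0.353 = 94% of them stop there.

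**The case against.** Four objections deserve weight.

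- **The text does not state that the listed order is binding, or that a failed step ends testing.** It could describe two levels only: the gate, then the three pairs. The article condenses a fuller protocol, and the analysis plan is not shown. This is fair, and the point is therefore conditional on the fixed-sequence reading. That is still the ordinary meaning of hierarchical testing followed by a list. If two levels were meant, the replacement sentence merely says so.
- **The order follows the stated priorities.** The Discussion puts superiority over conventional treatment first and timing second, and testing each timing against control before comparing the two is a valid procedure. This stands as a reason why the plan is not invalid. It does not justify the order, because the parallel tests keep every rejection that the sequence makes.
- **The order is not the main obstacle at the planned effect.** This stands. When one timing alone has the 20.2-point effect, the pooled gate removes more power than the order does, and without the order the timing result is still missed in about 72% of trials.
- **The loss is not uniform.** This also stands. When both timings work well and differ (50/90/70%), the sequence still succeeds in 73% of trials. The 75% at 50/80/60% rests on a 30-point preoperative effect that the documents do not contain.

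A reader might infer that the timing question cannot be examined at all. The documents do not support that: only the confirmatory test is barred, and nothing prevents reporting the difference with a confidence interval.

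**Conclusion.** The point holds on the fixed-sequence reading. A confirmatory timing test is seldom reached when one timing is close to control: about 1% significant against 28% in parallel at 50/70.2/50%, and 17% against 75% at an assumed 50/80/60%, with 90 per arm. The order also costs 10 points for postoperative versus control (79% to 69%) when both timings have the planned effect. Neither loss buys any type I error protection beyond the gate.

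The figures assume equal arms, the rates shown and unstratified z tests in place of the centre-stratified test. With 112 per arm the pattern is the same.

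This should be fixed, but it is not a fault in the primary analysis. A reader might go further and conclude that the primary result is compromised or that the pooled gate must be replaced. The documents do not support either conclusion: the pooled test and its error rate are untouched, and it is the comparison that the trial chose and powered.

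**What to change.** Before unblinding, replace the hierarchical sentence with:

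*If the pooled test is significant, the three pairwise comparisons are each tested at two-sided 0.05, in no order (closed testing for three arms).*

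This is a change of wording. It needs no further patients, adds no family-wise error and loses no rejection. Because recruitment is under way, the change should be dated and made without sight of outcome data by arm. If it is made as a protocol revision, the Ethical plan section's own requirements (ethics committee approval and renewed consent) would apply. If the analysis plan already sets the pairwise tests out in this way, it is enough to bring the protocol wording into line.

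Replacing the pooled gate with a three-arm, 2-df test is not part of this fix. At the planned difference its power would be about 84% if both timings work and 82% if only one does, against 90% and 35% for the pooled gate. It would change the primary null hypothesis and the powered comparison, so it is a trade-off for the sponsor to weigh separately.
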